### 7.5. Secondary outcomes – survival

Survival over the study period will be examined using Cox proportional hazard model adjusted for factors in the minimisation algorithm with survival curve going beyond 12m if there is enough data available according to Pocock SJ, Clayton TC, Altman DG. Survival plots of time-to-event outcomes in clinical trials: good practice and pitfalls. *Lancet* 2002;**359**:1686-9.

### 7.6. Pre-specified sub group analysis

Comparison of mRS at 6-months based on Ordinal analysis will be split by the following sub-groups: age [<70, ≥70], baseline probability of being alive and independent at 6-months [<0.15, 0.16-1 based on Carls model], type of stroke [ischaemic, haemorrhagic], patient able to provide own consent [yes, no] adjusting for baseline motor impairment [yes/no], baseline aphasia [yes/no] and baseline depression [yes/no].

Motor impairment: In patients with motor impairment resulting from the initial stroke [where motor impairment is defined as above] is there a difference in the motor function at 6 months [as measured by SIS, question 12, 17, 18 on follow up)]. Is this maintained at 12 months? Linear regression analysis will be performed on the baseline to 6-month change and separately for the 6-month to 12-month change both unadjusted and also adjusted for factors in the minimisation.*.*

Communication impairment: In patients with communication impairment resulting for the initial stroke [where communication impairment is defined as above on NIHSS] is there a difference in the communication function at 6 months [as measured by SIS, question 15]. Is this maintained at 12 months? This analysis will be performed unadjusted and also adjusted for factors in the minimisation.

Linear regression analysis will be performed on the baseline to 6-month change and separately for the 6-month to 12-month change both unadjusted and also adjusted for factors in the minimisation.

Mood: Is there a relationship between outcome [as defined by mRS at 6-months] and mood [measured using MHI5] and is this relationship affected by Fluoxetine?

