**Pre-defined subgroups**

The mRS will be compared at six months with an ordinal analysis in the following subgroups:

- Age (≤70, > 70yrs)
- Baseline probability of a good outcome on mRS (Counsell 2002) – to see if effects remain constant across the range of stroke severities (<0.15 vs 0.15-1 probability of being alive and independent at 6 months)
- Ischaemic vs haemorrhagic stroke
- Patient who were unable to consent for themselves since this subgroup will allow us to answer the question whether routine use of fluoxetine is likely to benefit patient in whom a formal assessment of mood is impossible because of communication and cognitive problems.

In addition we are particularly interested to know whether the effect of treatment on neurological function is modified by specific neurological deficits present at baseline. Because patients may have a combination of neurological deficits, individual patients may appear in more than one subgroup

Patients with a motor deficit (i.e. weakness or clumsiness on NIHSSS) affecting face, arm or leg.

- Relevant outcomes – SIS – Strength, mobility, hand/arm function
- Patients with aphasia based on the NIHSS
- Relevant outcomes – SIS - communication

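### The plan asks whether the treatment effect is constant across severity and modified by baseline deficits, but prespecifies no interaction or other heterogeneity estimate; for motor deficit and aphasia it has no comparison group

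*SAP*

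**What the plan says.** SAP Section 3, under the pre-defined subgroups, states two aims about variation in the treatment effect. The subgroup defined by predicted outcome is included "to see if effects remain constant across the range of stroke severities". For motor deficit and aphasia, the authors want to know "whether the effect of treatment on neurological function is modified by specific neurological deficits present at baseline".

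The methods are these:

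- **Section 3:** "The mRS will be compared at six months with an ordinal analysis in the following subgroups". The factors are age, predicted outcome, stroke type and inability to consent.
- **Section 7.6, mRS:** "Comparison of mRS at 6-months based on Ordinal analysis will be split by the following sub-groups". The same four factors follow, each with two levels, and then three covariates: baseline motor impairment, aphasia and depression.
- **Section 7.6, motor function:** the question is put "In patients with motor impairment resulting from the initial stroke", with SIS motor items as the outcome.
- **Section 7.6, communication:** the question is put "In patients with communication impairment resulting for the initial stroke", with the SIS communication item as the outcome.

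The motor and communication models are linear regressions, run unadjusted and adjusted for the minimisation factors.

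**The concern.** Whether an effect differs between groups of patients is a question about the difference between two treatment effects. Section 7.6 plans the separate effects and never their difference. If those results are all that is reported, a subgroup with a small p-value beside one with a large p-value invites the conclusion that fluoxetine works in one and not in the other, even when the effect is the same in both.

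The motor and aphasia questions have a further problem. A treatment effect estimated only in patients with aphasia cannot show whether aphasia changes the effect, because nothing is estimated in patients without it. This is the question in which the SAP declares particular interest.

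**Working it through.** **1. Aim against method.**

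| Factor | Aim in Section 3 | Planned in Section 7.6 | Can modification be judged? |
|---|---|---|---|
| Predicted outcome | Constancy across severity | mRS effect in each level | Both levels estimated; no contrast planned |
| Age, stroke type | None stated | mRS effect in each level | Both levels estimated; no contrast planned |
| Own consent | Benefit in those unable to consent | mRS effect in each level | Not the stated aim; the within-group estimate is legitimate |
| Motor deficit | Modification of effect | SIS motor outcomes in patients with the deficit only | No; there is no comparator |
| Aphasia | Modification of effect | SIS communication in patients with the deficit only | No; there is no comparator |

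**2. Does another section supply the missing contrast?** No.

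- Section 7.4 compares the SIS domains by linear regression adjusted for the minimisation factors. Motor deficit and aphasia enter as main effects, which say nothing about modification.
- The mood question at the end of Section 7.6 asks whether a relationship is affected by treatment. However, the MHI-5 is scheduled only at follow-up (Section 4.2), so it is not a baseline subgroup factor, and no model is named.

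**3. Illustrative size.** The SAP has no figure to reproduce. Assumptions, none taken from the SAP: two-sided 0.05; overall power 80% or 90%; the same effect in both subgroups; normal approximation.

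- Mean of the overall z statistic: d = 1.960 + z(power). This is 1.960 + 0.842 = 2.802 at 80%, and 1.960 + 1.282 = 3.242 at 90%.
- A subgroup with share s of the patients has mean z of d√s. Its power is P(|Z| > 1.96) at that mean.
- With powers a and b in the two subgroups, P(exactly one significant) = a(1 − b) + b(1 − a).

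| Overall power | Split | Power in each subgroup | Exactly one significant |
|---|---|---|---|
| 80% | 50:50 | 0.508, 0.508 | 2 × 0.508 × 0.492 = 0.50 |
| 90% | 50:50 | 0.630, 0.630 | 2 × 0.630 × 0.370 = 0.47 |
| 80% | 20:80 | 0.240, 0.707 | 0.240 × 0.293 + 0.707 × 0.760 = 0.61 |
| 90% | 20:80 | 0.305, 0.826 | 0.305 × 0.174 + 0.826 × 0.695 = 0.63 |

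In all four rows a valid interaction test of that factor signals heterogeneity with probability 0.05.

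**4. What the interaction test costs.** SE(interaction)/SE(overall) = 1/√(s(1 − s)). This is 2.0 for a 50:50 split and 2.5 for 20:80. Power to detect an interaction as large as the overall effect is then 0.29 to 0.37 (50:50) or 0.20 to 0.25 (20:80), at 80% to 90% overall power. Four interaction tests, treated as independent, carry a chance of 1 − 0.95⁴ = 0.19 of at least one false positive.

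**The case against.** Five points can be made for the plan.

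- **The mRS subgroups do not make modification unknowable.** This stands. Both levels of each factor are estimated, so a ratio of odds ratios could be derived afterwards. A reader might infer that the plan can never show modification for these factors, but the text does not support that. The defect is that the contrast is not prespecified.
- **Not every subgroup asks about modification.** This also stands. The consent subgroup is about benefit within that group, and age and stroke type carry no stated question. Section 7.6 itself words the motor and communication questions as within-group questions, so for these two the fault is a mismatch with Section 3.
- **The covariates.** A reader might infer that the subgroup models abandon two of the four minimisation factors. That is wrong for the motor and communication models, which have a version adjusted for all of them. For the mRS subgroups, the SAP does not say whether the three listed covariates supplement or replace the minimisation factors. It needs a clarifying sentence, but it does not bear on modification.
- **Interaction tests do not remove multiplicity.** Correct. With no effect anywhere, the chance that at least one of the eight within-subgroup mRS tests is positive is about 0.25 to 0.26 by simulation (four independent 50:50 splits). The like-for-like figure is 0.19 for four interaction tests, not 0.05 for one. The case for an interaction term rests on the uniform-effect figures.
- **The harm is assumed.** Partly so. Section 7.6 sets no significance rule for subgroups and does not say that p-values will be compared across them. The probabilities show what such a reading would do; they do not show that the authors intend it.

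**Conclusion.** The point holds in two strengths. For motor deficit and aphasia, the question in Section 3 cannot be answered by the analysis in Section 7.6, because patients without the deficit are left out. This rests on the text alone and needs no assumption. For the mRS subgroups, and above all for severity where constancy of effect is the declared aim, the plan yields the separate effects but prespecifies no estimate of their difference.

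The discordance probabilities of 0.47 to 0.63 against 0.05 depend on the assumed power, significance level and splits, and illustrate scale only. The primary analysis is unaffected. The SAP should be changed, because the subgroup conclusions it promises are not supportable as planned.

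**What to change.** 1. **mRS subgroups.** For each of the four factors, fit the proportional-odds model in all patients with a treatment-by-subgroup term. Report the interaction as a ratio of odds ratios, with 95% CI and p-value, beside the within-subgroup odds ratios. Label these results exploratory. Keep the within-group estimate for patients unable to consent, since it answers that subgroup's stated aim.
2. **Motor deficit and aphasia.** Fit each relevant 6-month SIS domain score in all survivors with a treatment-by-deficit term. Report the interaction with its CI, and take the deficit-only treatment effect from the same model. Use the 6-month score because Section 4.2 schedules the SIS only at weeks 26 and 52, so the baseline-to-6-month change named in Section 7.6 has no baseline value.
3. **Covariates.** State whether motor impairment, aphasia and depression are added to the minimisation factors or replace them in the mRS subgroup models.
4. **Limits to state in the SAP.** Interaction power is low. Patients without the deficit may score near the top of the SIS domain, so an additive interaction could reflect a ceiling. Four mRS interaction tests carry about a 0.19 chance of at least one false positive, and the SIS interactions add to it.

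The cost is some SAP wording and a few model terms. No new data are needed: Section 4.1 makes motor deficit and aphasia minimisation factors, so both are recorded for every patient.

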## 4. Study Methods

### 4.1. Randomisation and blinding

Having obtained consent, the randomising person collects the baseline data necessary to complete a randomisation form and enters the patient’s baseline data into our computerized central randomisation service by means of a secure 24/7 Web interface or a telephone call to the trial office during office hours. After the computer program has checked these baseline data for completeness and consistency it allocates that patient a unique study identification number and a treatment pack number which corresponds to either Fluoxetine or Placebo. The system applies a minimisation program to achieve balance for four factors:

- Delay since stroke onset [2 – 8 days v 9 – 15 days]
- Predicted outcome at 6 months based on Counsell 2002 [predicted probability of being alive & independent at 6 months of 0 – 0.15 v 0.16 – 1]
- Presence of a motor deficit [yes v no – where deficit is NIHSS5 (right or left) >0, NIHSS6 (right or left)>0 or NIHSS7 >0]
- Presence of aphasia [NIHSS question 9: 0 v 1 – 3 ]

The minimisation algorithm randomly allocates the first patient to a treatment, but allocates each subsequent patient to the treatment that leads to the least difference between the treatment groups with respect to the prognostic factors (Altman 2005). To ensure that we retain a random element to treatment allocation, patients will be allocated to the group which minimizes differences between groups with a probability of 0.8. The system contains a list of treatment codes for each centre and which match the stocks held at that centre. At the end of the session each patient is allocated a treatment code which corresponds to either an active (f.luoxetine 20mg once daily) or placebo treatment pack which contains six months supply of capsules held at that centre. The randomisation system will take account of the drug stocks held locally to firstly ensure the allocated treatment is available and second to minimise wastage.

The patient, their families, the healthcare team including the pharmacist and anyone involved in outpatient assessments will be blinded to the treatment allocation.

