### 4.3.6. Six Simple variable (SSV) model

Based on the work ‘C.Counsell, M.Dennis, M.McDowall,C.Warlow. Validation of New Prognostic Models Predicting Outcome After Acute and Subacute Stroke : Development and Validation of New Prognostic Models. *Stroke* 2002, 33:1041-1047’ we can calculate the probability of being alive and independent at 6-months using the following model:

[figure not shown]

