## 7. Final analysis

### 7.1. Primary outcome

Comparison of Modified Rankin score [mRS] at six-months post randomisation by treatment group where mRS treated in its full ordinal format [scores of 0,1,2,3,4,5,6]. This will be examined using an ordinal logistic regression and will be performed in both an unadjusted manner and also adjusted for factors in the baseline minimisation (as recommended by the Draft CPMP guidelines, December 2001). We will present common odds ratios using the proportional odds method and for the unadjusted analysis we will also present the individual dichotomies.

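### The predicted-outcome subgroup in SAP section 7.6 leaves patients at 0.15 in neither group, and conflicts with both the section 3 subgroup and the section 4.1 minimisation stratum

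*SAP*

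**What the plan says.** The SAP divides the predicted probability of being alive and independent at six months in three places.

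- Section 3, which restates the protocol's methods, defines the subgroup as "<0.15 vs 0.15-1 probability of being alive and independent at 6 months".
- Section 4.1 defines the minimisation factor as "predicted probability of being alive & independent at 6 months of 0 – 0.15 v 0.16 – 1".
- Section 7.6, the final-analysis text, defines the subgroup as "baseline probability of being alive and independent at 6-months [<0.15, 0.16-1".

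Section 4.3.6 gives the source of the variable: "we can calculate the probability of being alive and independent at 6-months using the following model". The model itself is in a figure that is not shown, and the readable text states no rounding rule. Section 7.1 says the primary analysis is "also adjusted for factors in the baseline minimisation", so the section 4.1 stratum is also a covariate.

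**The concern.** Two groups meant to divide the trial by predicted outcome should cover every patient once. Those in section 7.6 do not: the lower stops short of 0.15 and the upper starts at 0.16. A programmer who codes that line literally gets two groups that do not add up to the patients with an mRS, and nothing in the SAP gives a reason to leave out a band of predicted probability.

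The other two places do not settle where those patients belong, because they put 0.15 on opposite sides. Section 7.6 agrees with section 3 on the lower group and with section 4.1 on the upper group, and combining the two opens the gap. At stake is one pre-specified subgroup analysis of six-month mRS. It would lose some patients, or their placement would have to be decided by someone at the analysis stage.

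**Working it through.** **Inputs.** The three rules as printed in SAP sections 3, 4.1 and 7.6; the target of at least 3,000 patients from SAP section 2. There is no figure in the plan to reproduce.

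**Step 1: classify values near the cut.** Each rule is read as a pair of intervals and applied to the unrounded probability and to the probability rounded to two decimals.

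| Probability | Section 3 | Section 4.1 | Section 7.6 |
| --- | --- | --- | --- |
| 0.149 unrounded | low | low | low |
| 0.149 rounded to 0.15 | high | low | none |
| 0.15 exactly | high | low | none |
| 0.154 unrounded | high | none | none |
| 0.154 rounded to 0.15 | high | low | none |
| 0.156 unrounded | high | none | none |
| 0.156 rounded to 0.16 | high | high | high |
| 0.16 exactly | high | high | high |

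- Section 3 covers everyone under either reading.
- Section 4.1 covers everyone only if values are rounded to two decimals.
- Section 7.6 has a gap under both readings: 0.15 up to but not including 0.16 if unrounded, and recorded 0.15 (about 0.145 to 0.155 before rounding) if rounded.
- At exactly 0.15 the three rules give high, low and neither.

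**Step 2: how many patients.** The SAP gives no distribution of the probability, so this is illustration only. For a distribution function F, the share in the unrounded gap is F(0.16) − F(0.15), and the count is 3,000 times that share.

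- Uniform on 0 to 1: 0.16 − 0.15 = 0.0100, or 30 patients. The share below 0.15 is 0.15, so the gap is 0.0100/0.15 = 6.7% of the size of the low group.
- Beta(1,2), with F(x) = 1 − (1 − x)²: 0.85² − 0.84² = 0.7225 − 0.7056 = 0.0169, or about 51 patients. The share below 0.15 is 1 − 0.7225 = 0.2775, so the gap is 6.1% of the size of the low group.
- Logit-normal, mean −1 and SD 1: logit(0.15) = −1.735 and logit(0.16) = −1.658, so the share is Φ(−0.658) − Φ(−0.735) = 0.2552 − 0.2313 = 0.0239, or about 72 patients. The gap is 0.0239/0.2313 = 10.3% of the size of the low group.

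Under the rounded reading the band is 0.145 to 0.155, also 0.01 wide, and the same three distributions give about 30, 51 and 72. The illustrative range is therefore about 1.0 to 2.4% of patients. These are not bounds: the answer depends on which distribution is assumed.

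**The case against.** The strongest reply is that this is a slip of one symbol. If the lower group in section 7.6 was meant to include 0.15, the section would match section 4.1, and with two-decimal values the gap would close. That is probably what happened. But the document does not say so, section 3 points the other way, and rounding does not repair section 7.6 as printed.

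It can also be said that section 3 only restates the protocol and should not count against the SAP. That has some force, and only sections 3 and 7.6 define a subgroup at all; section 4.1 defines a minimisation factor. A reader might infer three competing subgroup definitions, but there are two, plus a stratum. Even with section 3 set aside, sections 4.1 and 7.6 disagree on the lower group.

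A reader might also infer that a subgroup has to coincide with a minimisation stratum. The SAP does not work that way: age, stroke type and ability to consent are subgroups without being minimisation factors. The reason to align here is narrower. The same predicted probability is used both as covariate and as subgroup, and one definition is cleaner than two. The upper groups in sections 4.1 and 7.6 are already worded identically.

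Finally, a reader might infer that the cut could be chosen to suit the result. The wording leaves that open in principle, but nothing in the documents suggests such an intention, and no calculation here shows that moving so narrow a band would change a subgroup conclusion.

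**Conclusion.** The point stands as a definite but small defect. Section 7.6 omits patients at 0.15 under either reading of the variable, and the two other places in the SAP give opposite answers for them. The omission and the conflict follow from the printed rules alone and need no assumption.

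The number of patients does need one. It cannot be derived from the SAP; roughly 1 to 2.5% is the range under illustrative distributions, and no specific count should be quoted as the trial's own.

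The stronger reading, that the primary result is compromised, is not supported. The primary comparison in section 7.1 does not use the section 7.6 groups. The section 4.1 wording has a gap of its own if values are unrounded, but the allocation program had to place every randomised patient in order to minimise on this factor. That calls for confirming how the program cut the variable; it does not show that patients are lost from the adjusted analysis.

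**What to change.** Before unblinding:

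1. Confirm with those who run the randomisation system where it cut the probability and whether it rounded first. The SAP does not say whether the stratum itself is stored; if it is not, it can be recomputed with the confirmed rule.
2. Define the subgroup in section 7.6 by those same two strata, written as complementary inequalities with the rounding stated. As section 4.1 is worded, 0.15 is in the low group, so the expected form is ≤0.15 v >0.15 on the probability as rounded by that system. If the check shows a different rule, the wording should follow the system. Applying this form to unrounded values could move patients: 0.152 rounds to 0.15 and is low, but unrounded it would be high.
3. Use that same variable as the adjustment covariate for this factor, and state the cut and rounding in section 4.1.
4. Note in the SAP that this replaces the protocol wording restated in section 3, rather than silently rewriting section 3, so that the SAP does not drift from the protocol without a record.

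The cost is a few lines of SAP text and one query about the randomisation program. No new data are needed and the design does not change.

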## 3. Statistical methods from protocol

Our primary analyses will retain patients in their original assigned treatment groups.

Our primary analysis will compare the mRS at the six month follow up using an ordinal analysis adjusted for any baseline imbalance in those factors included in our minimisation algorithm.

We will compare the mRS at the twelve month follow up to establish if any benefits observed at 6 months are maintained.

Secondary analyses will compare the two treatment groups with respect to the following outcomes at 6 and 12 months.

- Survival (Logistic regression)
- EQ5D-5L (HRQOL) to generate utilities
- SIS (for each of 9 domains on which the patient scored 0-100)
- MHI 5 (mood)
- Fatigue (Vitality subscale of SF36)
- New diagnosis of depression requiring treatment with antidepressants
- Adverse events
- Adherence to trial medication

Longer term survival will be analysed with Cox proportional hazards model

We will also perform analyses of potential mediating factors e.g. the role of depression. We will seek to answer the question whether any benefits are mediated by improvement in mood (based on MHI 5 and also whether any apparent loss of benefits in mRS or SIS between 6 months to 12 months is because of a deterioration in mood.

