### 4.2. Study Assessments

|  | Days | Weeks | | | | | | | |
| --- | --- | --- | --- | --- | --- | --- | --- | --- | --- |
| **Assessment** | 2-15 | 4-6 | 12 | 24 | 26 | 30 | 50 | 52 | 54 |
| ***Local*** |  |  |  |  |  |  |  |  |  |
| Screen of eligibility | x |  |  |  |  |  |  |  |  |
| Check results of post stroke bloods | x |  |  |  |  |  |  |  |  |
| Give PIB to patient and/or carer | x |  |  |  |  |  |  |  |  |
| CONSENT | x |  |  |  |  |  |  |  |  |
| Collect baseline data | x |  |  |  |  |  |  |  |  |
| Randomise | x |  |  |  |  |  |  |  |  |
| Record treatment code/study no. | x |  |  |  |  |  |  |  |  |
| Prescribe study medication | x |  |  |  |  |  |  |  |  |
| Dispense 6 months of treatment | x |  |  |  |  |  |  |  |  |
| FAX no. of dispensed medication | x |  |  |  |  |  |  |  |  |
| Complete discharge form including |  | + |  |  |  |  |  |  |  |
| Adverse events |  | + |  |  |  |  |  |  |  |
| All medications |  | + |  |  |  |  |  |  |  |
| Adherence |  | + |  |  |  |  |  |  |  |
| Updated contact details |  | + |  |  |  |  |  |  |  |
| ***Central (postal or telephone)*** |  |  |  |  |  |  |  |  |  |
| Email/fax notification of allocation | x |  |  |  |  |  |  |  |  |
| Letter informing GP of participation | x |  |  |  |  |  |  |  |  |
| 1 month follow up for outpatients |  | o |  |  |  |  |  |  |  |
| 3 month prompt to patients |  |  | x |  |  |  |  |  |  |
| GP Questionnaire |  |  |  | x |  |  | x |  |  |
| Adverse events |  | o |  | x |  |  |  |  |  |
| Follow up on previous AEs |  |  |  | x |  |  | x |  |  |
| All medications |  | o |  | x |  |  | x |  |  |
| Adherence |  | o |  | x |  |  |  |  |  |
| Resource use |  |  |  | x |  |  | x |  |  |
| Patient follow up |  |  |  |  |  |  |  |  |  |
| Adverse events |  | o |  |  | x |  |  |  |  |
| Follow up on previous AEs |  |  |  |  | x |  |  | x |  |
| Adherence |  | o |  |  | x |  |  |  |  |
| modified Rankin scale |  |  |  |  | x |  |  | x |  |
| Stroke Impact Scale |  |  |  |  | x |  |  | x |  |
| Mental health inventory 5 |  |  |  |  | x |  |  | x |  |
| EQ5D-5L (HRQOL) |  |  |  |  | x |  |  | x |  |
| SF36 Vitality subscale |  |  |  |  | x |  |  | x |  |
| Resource use |  |  |  |  | x |  |  | x |  |
| Retrieve residual capsules (pill count, reconciliation and destruction) |  |  |  |  | x |  |  |  |  |

+ - only for patients enrolled as inpatients

o - only for patients enrolled as outpatients

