### 6.3. Success of minimisation, and baseline data

**Minimisation**: Check minimisation is successfully balancing on minimisation factors.

**Other baseline data [collected on randomisation form]:** Check treatment balanced by sex, ethnicity, whether patient is an inpatient, depression, diabetes, previous CHD, previous ischaemic stroke/TIA, previous intracranial bleeding, history of GI bleeding, hyponatraemia, bone fractures, current mood [both yes, 1 yes, none yes], recent intracerebral bleeding, type of stroke/OCSP classification and total NIHSS.

**Other data collected post treatment [collected on discharge form]:** Check the following are equally balanced by treatment group: final diagnosis of randomising event, post randomisation non-trial medication, discharge destination and in-hospital compliance variables for inpatients [received any trial medication, taking till death/discharge, reasons for not taken till death or discharge and doses missed].

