### 7.4. Secondary outcomes - continuous

Where the outcome of interest is continuous, these will be compared between treatment groups using linear regression adjusting for factors in the baseline minimisation, or an alternative approach as necessary. This analysis will be conducted for the following outcomes at both six and twelve months.

1. Quality of life as measured by the EuroQol [EQ-5D]
2. Depression and anxiety as measured by the mental health inventory 5 [MHI-5 – question 21,22 of 6-month follow up; question 17,18 of 12-month follow up] and SIS [question 14 on 6-month follow up; question 10 on 12-month follow up].
3. Fatigue as measured by the vitality sub-scale of the Short Form (36) Health Survey [SF-36 question 20 on 6-month follow up; question 16 on 12-month follow up].
4. Limb strength as measured by SIS [question 12 on 6-month follow up; question 8 on 12-month follow up].
5. Hand function as measured by SIS [question 18 on 6-month follow up; question 14 on 12-month follow up].
6. Cognitive function as measured by SIS [question 13 on 6-month follow up; question 9 on 12-month follow up].
7. Communication as measured by SIS [question 15 on 6-month follow up; question 11 on 12-month follow up].
8. Extended ADL as measured by SIS [question 16 on 6-month follow up; question 12 on 12-month follow up].
9. Mobility as measured by SIS [question 17 on 6-month follow up; question 13 on 12-month follow up].
10. Social activity as measured by SIS [question 19 on 6-month follow up; question 15 on 12-month follow up].
11. Overall patient outcome as measured by the SIS total score
12. Overall recovery as measured by SIS thermometer [question 28 on 6-month follow up; question 24 on 12-month follow up].

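### SAP 7.6 regresses the change in SIS from baseline to 6 months in the motor and communication subgroups, but the SAP shows no baseline SIS, so that regression cannot be computed

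*SAP*

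**What the plan says.** Section 7.6 defines two analyses within subgroups of patients who had a particular deficit at baseline.

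- **Motor.** The question is "is there a difference in the motor function at 6 months [as measured by SIS, question 12, 17, 18 on follow up", followed by whether any difference lasts to 12 months.
- **Communication.** The question is "is there a difference in the communication function at 6 months [as measured by SIS, question 15", with the same follow-on question.

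Both paragraphs then give the same method: "Linear regression analysis will be performed on the baseline to 6-month change and separately for the 6-month to 12-month change", unadjusted and adjusted for the minimisation factors.

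The section 4.2 schedule has this column order: "Assessment | 2-15 | 4-6 | 12 | 24 | 26 | 30 | 50 | 52 | 54". The first column is in days and the rest are in weeks. The SIS row reads "Stroke Impact Scale | | | | | x | | | x".

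Section 6.3 itemises the data collected on the randomisation form. The list ends with "recent intracerebral bleeding, type of stroke/OCSP classification and total NIHSS" and has no SIS item. Section 3 introduces the secondary outcomes, SIS among them, with "Secondary analyses will compare the two treatment groups with respect to the following outcomes at 6 and 12 months". Section 7.4 introduces the SIS domains with "This analysis will be conducted for the following outcomes at both six and twelve months" and gives question numbers for the 6-month and 12-month forms only.

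**The concern.** A change from baseline needs the same instrument at baseline and at follow-up. Section 7.6 asks for such a change in SIS, yet nothing in the SAP shows SIS being collected at baseline. If so, a method that the plan states twice cannot be carried out.

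Section 3 singles these subgroups out. It says the investigators particularly want to know whether specific deficits at baseline modify the treatment effect on neurological function. It names SIS strength, mobility and hand/arm function for the motor subgroup and SIS communication for the aphasia subgroup. Section 7.6 is where those analyses are specified. With no usable 6-month method there, someone must choose a substitute while the trial is running or after it ends. The candidates include the raw 6-month score and a score adjusted for baseline NIHSS. A pre-specified analysis is meant to avoid that choice.

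**Working it through.** The plan gives no figure to reproduce here. The check sets what section 7.6 needs against what the SAP says is collected.

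**1. When SIS is measured.** Reading the SIS row of section 4.2 against the column headings:

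| Column | Days 2-15 | Wk 4-6 | Wk 12 | Wk 24 | Wk 26 | Wk 30 | Wk 50 | Wk 52 | Wk 54 |
|---|---|---|---|---|---|---|---|---|---|
| SIS | – | – | – | – | x | – | – | x | – |

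The cell for days 2-15, the baseline visit, is empty.

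**2. Whether SIS is collected at baseline under another heading.** The schedule has a general row for collecting baseline data that is not itemised. Section 6.3 does itemise the randomisation form, and SIS is absent. SIS also has its own schedule row with no baseline mark. Sections 3 and 7.4 agree with this: both place SIS at 6 and 12 months only.

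**3. Whether NIHSS could supply the baseline value.** Section 4.1 defines motor deficit and aphasia from NIHSS items. Section 4.3.5 scores those items from 0 up to at most 4. Section 4.3.1 transforms SIS domains to a 0 to 100 scale. One cannot be subtracted from the other. A change in NIHSS itself is not available either, because the schedule shows no NIHSS assessment at follow-up. No motor or communication instrument is shown at both baseline and 6 months.

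**4. What can be computed.**

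| Quantity | Needs | Available? |
|---|---|---|
| Change, baseline to 6 months | SIS at baseline and week 26 | No |
| Difference between arms at 6 months | SIS at week 26 | Yes |
| Difference between arms at 12 months | SIS at week 52 | Yes |
| Change, 6 to 12 months | SIS at weeks 26 and 52 | Yes |

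**5. How many models are affected.** Section 7.4 treats strength (question 12 on the 6-month form), mobility (17), hand function (18) and communication (15) as separate outcomes. On that reading the count is 4 domains × 2 (unadjusted, adjusted) = 8 models. Section 7.6 does not say whether the three motor questions are modelled separately or together. If together, the count is 2 outcomes × 2 = 4.

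**6. Whether the intended comparison can be recovered.** Let D0, D6 and D12 be the differences in mean SIS between arms at baseline, 6 and 12 months, in the same patients. The difference in change from baseline is D6 − D0. Randomisation gives D0 an expected value of zero, so the expected difference in change equals the expected D6. A direct 6-month comparison therefore targets the same treatment effect. One caveat applies: section 5.1.3 restricts these scales to patients alive at follow-up, so the equality assumes that deaths do not make the surviving groups differ at baseline.

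**7. What the 6-to-12-month change gives.** In patients with both scores, the difference in that change is D12 − D6. Alone it gives neither D6 nor D12. A value of zero is compatible with a benefit that was kept and with no benefit at any time. Added to D6, it gives D12.

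**The case against.** The strongest reply is that little is lost. The questions in section 7.6 are about a difference at 6 months, which can be answered without a baseline score. Section 7.4 already specifies linear regression adjusted for the minimisation factors for all four domains at 6 and 12 months, and section 3 names the domains for each deficit. The natural fallback is that model, restricted to the subgroup. The 6-to-12-month change bears directly on maintenance. All of this stands, and it limits the point. It does not remove it: the stated method for the 6-month question is still impossible, and section 7.4 is written for all patients and allows an alternative approach where necessary.

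Three stronger readings are tempting, and the SAP does not support them.

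- **That the subgroup analyses as a whole cannot be run.** Only the baseline-change regression fails. The other half of the same sentence can be computed, as can the comparisons at 6 and 12 months.
- **That an unblinded statistician would pick the replacement.** Section 5.2.3 does say that the trial statistician is unblinded when preparing data monitoring committee reports. The same section provides a blinded statistician to consider statistical issues that arise during the trial. That safeguard reduces the risk of a data-driven choice. A written rule would remove the need to choose.
- **That the plan loses its answer on recovery of the baseline deficit.** The interest stated in section 3 is whether baseline deficits modify the treatment effect, which is a different question from recovery over time.

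The protocol is not at hand, so a baseline SIS described only there cannot be ruled out absolutely. It would contradict the SAP's own schedule, and the two would then have to be reconciled.

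**Conclusion.** The point holds for the change from baseline to 6 months in SIS, in both the motor and the communication paragraph. As written, that analysis has no outcome variable. It affects 8 models if the four domains are analysed separately, or 4 if the motor questions are combined. The conclusion rests on the SAP's schedule and its list of baseline data, which agree with each other and with sections 3 and 7.4. It needs no numerical assumption.

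The consequence is limited. These are subgroup analyses of secondary outcomes, and the primary mRS analysis does not depend on them. The intended treatment comparison can be recovered from data already scheduled. No loss of precision can be attributed to the error, because the SAP gives no correlation between baseline NIHSS and later SIS. The text should still be corrected before the final analysis, because an analysis that is specified twice cannot be carried out.

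**What to change.** In both the motor and the communication paragraph of section 7.6, replace the baseline-change wording with text to this effect:

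> Within the deficit subgroup, each relevant SIS domain score will be compared between arms by linear regression at 6 months and, separately, at 12 months, unadjusted and adjusted for the minimisation factors, as in section 7.4. The change from 6 to 12 months will be reported as supportive evidence on maintenance.

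State that strength, mobility and hand function are analysed as separate domains, if that is the intention. Give the question numbers for both forms, since they differ. Section 7.4 lists them as follows (6-month form, then 12-month form): strength 12 and 8, mobility 17 and 13, hand function 18 and 14, communication 15 and 11.

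Adjusting in addition for the baseline NIHSS item score for the deficit is optional. It is not needed to correct the error. If it is wanted, first confirm that item scores are held, and not only the yes/no minimisation factor, and name the items in advance.

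The cost is a wording change to the SAP. It needs no new data and leaves the primary analysis as it is.
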